# Arthritis prevention in the pre-clinical phase of RA with abatacept (the APIPPRA study): a multi-centre, randomised, double-blind, parallel-group, placebo-controlled clinical trial protocol

**DOI:** 10.1186/s13063-019-3403-7

**Published:** 2019-07-15

**Keywords:** Rheumatoid arthritis, At risk, Pre-clinical phase, Intervention, Abatacept, Double-blind, Antibodies to citrullinated protein antigens, Autoantibodies, Placebo-controlled, Randomised

## Abstract

**Trial design:**

We present a study protocol for a multi-centre, randomised, double-blind, parallel-group, placebo-controlled trial that seeks to test the feasibility, acceptability and effectiveness of a 52-week period of treatment with the first-in-class co-stimulatory blocker abatacept for preventing or delaying the onset of inflammatory arthritis.

**Methods:**

The study aimed to recruit 206 male or female subjects from the secondary care hospital setting across the UK and the Netherlands. Participants who were at least 18 years old, who reported inflammatory sounding joint pain (clinically suspicious arthralgia) and who were found to be positive for serum autoantibodies associated with rheumatoid arthritis (RA) were eligible for enrolment. All study subjects were randomly assigned to receive weekly injections of investigational medicinal product, either abatacept or placebo treatment over the course of a 52-week period. Participants were followed up for a further 52 weeks. The primary endpoint was defined as the time to development of at least three swollen joints or to the fulfilment of the 2010 American College of Rheumatology/European League Against Rheumatism (ACR/EULAR) classification criteria for RA using swollen but not tender joints, whichever endpoint was met first. In either case, swollen joints were confirmed by ultrasonography. Participants, care givers, and those assessing the outcomes were all blinded to group assignment. Clinical assessors and ultrasonographers were also blinded to each other’s assessments for the duration of the study.

**Conclusions:**

There is limited experience of the design and implementation of trials for the prevention of inflammatory joint diseases. We discuss the rationale behind choice and duration of treatment and the challenges associated with defining the “at risk” state and offer pragmatic solutions in the protocol to enrolling subjects at risk of RA.

**Trial registration:**

Current Controlled Trials, ID: ISRCTN46017566. Registered on 4 July 2014.

**Electronic supplementary material:**

The online version of this article (10.1186/s13063-019-3403-7) contains supplementary material, which is available to authorized users.

## Background

Rheumatoid arthritis (RA) is a common chronic inflammatory immune-mediated disease of joints afflicting more than 500,000 subjects in the UK [1, 2]. If not adequately treated, the condition leads to destruction of synovial joints and significant disability. RA is costly to individuals and their families; one third of patients with arthritis stop work within 2 years of onset because of the deterioration in quality of life associated with their disease [3]. In the UK, RA is costly to the economy; the cost is estimated to be in the region of £5 billion per year through direct costs to the National Health Service (NHS) and associated healthcare providers and indirect costs associated with early mortality and loss of productivity [4].

The introduction of therapeutic strategies that focus on early, intensive treatment with conventional synthetic and biological disease-modifying anti-rheumatic drugs (DMARDs) has transformed the treatment of RA. Clinical trials have demonstrated that this approach leads to higher proportions of patients achieving periods of sustained clinical remission. This is associated with improved function and slowing or even prevention of joint damage over time. Indeed, intensive “treat-to-target” strategies in patients with very early RA can lead to extended periods of drug-free remission in a subset of patients [5]. If the pre-clinical phase of disease could be defined with accuracy, targeting therapy to those at highest risk of developing disease would have the potential to prevent or at the very least delay the onset of RA. Were such an approach to be successful, the disabling symptoms and signs of arthritis and the potential risks of unemployment could be prevented. Furthermore, the development of potentially life-threatening co-morbidities associated with chronic inflammatory diseases, such as cardiovascular disease and infection, could be substantially reduced.

The combination of serum antibodies to citrullinated protein antigens (ACPAs) and joint pain (termed arthralgia), in the absence of clinically detectable synovitis, is considered to most accurately define subjects at high risk of progressing to RA [6–8]. Data from longitudinal observational cohorts indicate that about 40% of high-risk subjects progress to clinically apparent arthritis within 18 months [9]. The combination of IgM rheumatoid factor (RF) and high serum ACPA levels defines those at highest risk; recent unpublished data indicate that the risk of developing disease in subjects with high titre ACPA in the absence of RF may be comparable to that in ACPA^+^RF^+^ subjects [9]. It follows from this that ACPA^+^RF^+^ or ACPA^+^RF^−^ arthralgia individuals would provide a valid target population for therapeutic intervention aimed at prevention of the syndrome we recognise as RA.

Abatacept is a fusion protein composed of the Fc region of the immunoglobulin IgG1 fused to the extracellular domain of cytotoxic T-lymphocyte antigen 4 (CTLA-4) [10]. Specifically, abatacept, a first-in-class co-stimulatory blocker, is a biologic DMARD that targets immune reactions early in the chain of events leading to inflammation in RA. It functions by interrupting the interaction between T cells and antigen-presenting cells, attenuating the co-stimulatory signals required for T-cell activation, differentiation and effector responses [11]. This results in downstream immunomodulatory effects on other inflammatory cells of the immune system.

In patients with established RA, administration of abatacept is associated with statistically significant and clinically meaningful improvements in the signs and symptoms, physical function and health-related quality of life. It inhibits structural damage in a broad spectrum of patients [12, 13], including those with early or established disease [14] and those with an inadequate response to tumour necrosis factor (TNF) blockade [15]. Interestingly, disease activity scores (DASs) have been shown to continue to improve beyond 12 months, indicating that the beneficial effects of co-stimulatory blockade not only are sustained but accumulate over extended periods of time.

In the ADJUST study, abatacept demonstrated good efficacy in patients with very early RA, including ACPA^+^ patients with undifferentiated arthritis, delaying onset of RA when compared with placebo, and promoting sustained remission rates and reduced radiographic progression, even after therapy is withdrawn [16]. More recent phase III studies have confirmed the efficacy of weekly subcutaneous (SC) injections of abatacept [17]. Clinical efficacy as measured by American College of Rheumatology 20 (ACR 20) and Health Assessment Questionnaire (HAQ) response was similar between SC abatacept and intravenous (IV) abatacept. Clinical trials and post-marketing surveillance suggest that the drug has an acceptable safety profile, particularly with respect to infection.

Although abatacept has a very favourable safety profile, suggesting that this approach might be acceptable to individuals during the pre-clinical phase of RA, there were no published studies at the time of APIPPRA (Arthritis Prevention In the Pre-clinical Phase of RA with Abatacept) study protocol development investigating the acceptability of targeted treatment strategies during the pre-clinical phase of RA. Therefore, understanding the factors that influence the acceptability of this therapeutic approach and the willingness of at-risk subjects to participate in interventional studies will be fundamental to trial methodology and the success of preventative, personalised medicine in the future.

## Methods/Design

### Study objectives

The principal objective of the study is to determine whether RA can be prevented or delayed if targeted immunotherapy is administered to subjects in whom autoantibody screening indicates a high risk of developing disease. Specifically, this study will test the hypothesis that the onset of arthritis in an “at risk” group can be prevented or delayed by weekly injections of abatacept for a period of 52 weeks.

The specific aims of study are to do the following:Evaluate the feasibility, efficacy and acceptability of abatacept therapy in subjects at high risk of developing RA andCharacterise immune and inflammatory responses associated with ACPA before, during and after therapy with abatacept.

### Trial design

The APIPPRA trial is a randomised, placebo-controlled, double-blind multi-centre trial undertaken at 31 specialist rheumatology clinics across the UK and the Netherlands. The trial was designed to ascertain the effectiveness of abatacept in ACPA^+^RF^+^ or ACPA^high^RF^−^ subjects with arthralgia who are deemed to be at high risk of developing RA. Eligible subjects will be randomly allocated to receive weekly injections of either abatacept or placebo treatment over the course of a 52-week period. This provides the best chance of establishing whether differences observed between the two groups are due to the treatment.

The SPIRIT checklist is included as (Additional file 4). The study design is shown in Fig. 1.

**Fig. 1 Fig1:**
[figure not shown]
Study design and flow chart

### Study population

The APIPPRA study will recruit study subjects who are at high risk of developing RA and who show no clinical evidence of joint swelling. Participants may be recruited by using a range of ethically approved methods, including during rheumatology out-patient clinics, following referral to recruiting centres from other rheumatology out-patient clinics, referrals from general practitioner (GP) practices through the routine referral pathway or patient identification centre (PIC) pathway, or through existing research databases and registries. Subjects may be identified by pre-screening of laboratory results for RF and ACPA.

### Eligibility criteria

#### Inclusion criteria

Male or female subjects who are at least 18 years old.Arthralgia, defined as non-traumatic joint pain localised to synovial joints, including (but not necessarily confined to) hands, wrists or feet and considered (by the supervising rheumatologist) to be inflammatory in nature.Positive for serum RF and ACPA as defined by local clinical laboratory testing. Subjects who are RF-negative but who carry high levels of serum ACPA (defined as being at least 3 × upper limit of normal [ULN] for the assay) may be included.Able and willing to give written informed consent and comply with the requirements of the study protocol (Additional file 1).

#### Exclusion criteria

Target disease exceptions:Previous diagnosis of RA or other form of inflammatory arthritis, including (but not limited to) systemic lupus erythematosus, psoriatic arthritis, ankylosing spondylitis, gout or pyrophosphate arthropathy and including current treatment with DMARDs or biological therapy.Arthralgia that, in the opinion of the supervising physician, is poorly localised (e.g., pelvic or shoulder girdle pain, pain that is confined to the axial skeleton or entheses, or pain which the physician considers to be due to osteoarthritis or fibromyalgia or related to other autoimmune conditions such as type I diabetes, coeliac or autoimmune thyroid disease).Clinically apparent inflammatory arthritis, as assessed by a rheumatologist, characterised by soft tissue swelling of one or more synovial joints. Subclinical synovitis, as detected by imaging modalities such as ultrasonography or magnetic resonance imaging, is not an exclusion criterion.A history of oral or parenteral use of corticosteroids within the last 12 weeks used to treat the current episode of musculoskeletal symptoms.Co-morbidities requiring chronic treatment with immunosuppressive or immune modulating therapy.Subjects who have at any time received treatment with any investigational drug within 28 days of the first dose of study drug.A history of acute allergic reactions to biological therapy or immunoglobulins.

Medical history and concurrent diseases:Subjects who are incapable of completing study-related assessments or give informed consent (see Additional file 1).Subjects with current symptoms of severe, progressive or uncontrolled renal, hepatic, hematologic, gastrointestinal, pulmonary, cardiac, neurologic or cerebral disease, whether or not related to RA and which, in the opinion of the investigator, might place a subject at unacceptable risk for participation in the study.Subjects with a history of cancer, other than non-melanoma skin cell cancers cured by local resection or carcinoma *in situ*, in the last 5 years.Subjects with tuberculosis (TB), including those at high risk of TB, chronic viral infections or recent serious bacterial infections; subjects receiving live vaccinations within 3 months of the anticipated first dose of study medication; or those with chronic illnesses that would, in the opinion of the investigator, put the participant at risk.Subjects who currently abuse drugs or alcohol.Subjects who are pregnant or breastfeeding or women of child-bearing potential not willing to use adequate contraception during the period of investigational medicinal product (IMP) dosing and for up to 14 weeks after the last dose of study drug.Male subjects not willing to use adequate contraception during the period of IMP dosing and for up to 14 weeks after the last dose of study drug.

##### Physical and laboratory tests at screening

Subjects must not test positive for the following:Latent tuberculous infection according to the interferon gamma release assay. Subjects who are positive and who have received treatment for at least 4 weeks may be selected.Antibodies to hepatitis B surface antigen.Hepatitis C antibody if the presence of hepatitis C virus was also shown with polymerase chain reaction or recombinant immunoblot assay.HIV.

Subjects with any of the following laboratory values or other test results that, in the opinion of the principal investigator, might place a subject at unacceptable risk for participation in the study:Haemoglobin < 85 g/LWhite blood cell count < 3 × 10^9^/LPlatelets < 100 × 10^9^/LSerum creatinine > 2 times the ULNSerum alanine transaminase (ALT) or aspartate aminotransferase (AST) > 2 times the ULN.

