#### Follow-up period (weeks 53–104)

Once participants have completed the 52-week course of IMP/placebo, they will be seen in the outpatient clinic every 3 months for assessments (see Table 1; Schedule of blood and urine sampling) similar to those in year 1 in order to monitor the impact of the treatment phase. This follow-up period is especially important because, if at any time participants develop new joint pains or swelling, they will be assessed promptly and treated appropriately in a similar way that clinical staff would assess any new patient presenting with similar symptoms.

**Table 1 Tab1:** Trial Flowchart and Schedule of Visits

Assessment		Study treatment				Follow up				
Visit No.^a^	1	2	3	4	5	6	7	8	9	10
WEEKS	Screening	Baseline	13	26	39	52	65	78	91	104
Registration Form	X									
Demographics	X									
Eligibility checks ^b^	X									
Medical History	X									
Physical Examination		X		X		X		X		X
Disease Activity Assessments		X	X	X	X	X	X	X	X	X
X-rays of hands & feet ^c^	X^c^									
Ultrasonography of symptomatic joints and limited joint set ^d^		X^d^		X^d^		X^d^		X^d^		X^d^
ACR/EULAR remission		X	X	X	X	X	X	X	X	X
IMP supply for weekly SC dosing ^e^		X	X	X	X					
Treatment Log (IMP)			X	X	X	X				
ESR & CRP ^f^	X		X	X	X	X	X	X	X	X
Routine Bloods (Haem & Biochem) ^g n^	X^g^		X	X	X	X	X^n^	X^n^	X^n^	X^n^
Screening Bloods (HIV, Hep B& C, TB) ^c^	X^c^									
Chest X-ray ^c^	X^c^									
Lifestyle Factors Questionnaire		X		X		X		X		X
Symptoms in Persons At Risk of Rheumatoid Arthritis (SPARRA) questionnaire ^h^		X^h^				X^h^				
Health Assessment Questionnaire (HAQ)		X	X	X	X	X	X	X	X	X
Modified Illness Perception Questionnaire (IPQ-R)		X		X		X		X		X
Euro-Quality of Life Questionnaire (EQ-5D)		X		X		X		X		X
Hospital Anxiety and Depression Scale (HADs)		X		X		X				X
Functional Assessment Of Chronic Illness Therapy-Fatigue Questionnaire (FACIT-F)		X		X		X		X		X
RA Work Instability Scale (RA-WIS)		X		X		X		X		X
Perceptions of Trial Participation Questionnaire ^i^	X^i^									
Concomitant Medication		X	X	X	X	X	X	X	X	X
Adverse Events		X	X	X	X	X	X	X	X	X
Compliance checks ^j^			X	X	X	X				
Status Form			X	X	X	X	X	X	X	X
Withdrawal Form ^k^			X^k^	X^k^	X^k^	X^k^	X^k^	X^k^	X^k^	X^k^
Blood/Urine for biomarkers ^l^		X	X	X	X	X	X	X	X	X

^a^Flexibility of scheduled visits will be allowed of +/- 2 weeks either side of visit

^b^Eligibility criteria

^c^These tests can be used if taken up to 12 weeks before screening

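### The only hepatitis B laboratory exclusion names the antibody to surface antigen, which marks immunity, and does not fit the article's exclusion of chronic viral infection

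*Protocol article*

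**What the plan says.** Three places in the protocol article bear on hepatitis B, and a fourth gives a useful comparison.

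- **Physical and laboratory tests at screening.** The list opens with "Subjects must not test positive for the following". Its hepatitis B item reads, in full, "Antibodies to hepatitis B surface antigen".
- **Same list, next item.** Hepatitis C is worded differently: "Hepatitis C antibody if the presence of hepatitis C virus was also shown with polymerase chain reaction or recombinant immunoblot assay".
- **Exclusion criteria, medical history and concurrent diseases.** Candidates with "chronic viral infections or recent serious bacterial infections" are excluded. No test is named.
- **Table 1, schedule of visits.** At screening the row "Screening Bloods (HIV, Hep B& C, TB)" is marked. Its footnote accepts results up to 12 weeks old at screening. No hepatitis B marker is given.

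**The concern.** Antibody to the surface antigen shows immunity, from vaccination or from an infection that has cleared. Current infection is shown by the antigen itself, and a chronic carrier is typically antigen-positive and antibody-negative. This is general laboratory knowledge; the article does not discuss it. The listed test therefore sorts people by immunity, while the stated aim elsewhere is to keep out people with infection.

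Two things are at stake. The first is safety: an unrecognised carrier would not fail the listed hepatitis B test and could be allocated weekly injections of an immunomodulator for 52 weeks. The second is recruitment: a site following the text would turn away volunteers only because they are immune. With 31 clinics in two countries, some sites may also have tested the antigen by local habit and others the antibody as written, so the eligibility rule may not have been the same everywhere.

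**Working it through.** No arithmetic applies. The criterion depends on no rate, power or event count, and the article gives no figure for hepatitis B carriage or vaccination. The check is to apply each rule as written to each kind of candidate.

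| Candidate | Laboratory list, hepatitis B item | Medical history: chronic viral infection | Result as written |
|---|---|---|---|
| Immune by vaccination or cleared infection (antibody positive, antigen negative) | Fails | Does not apply | Excluded |
| Neither marker present | Passes | Does not apply | Not excluded on hepatitis B |
| Carrier, already known or found (antigen positive, antibody negative) | Passes | Applies | Excluded |
| Carrier, unrecognised (antigen positive, antibody negative) | Passes | Applies in principle, but no stated test finds it | Not detected |

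The first and last rows are the problem. I then looked for text that would change either row.

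1. **Discretion.** The haematology and biochemistry limits that follow the list depend on the principal investigator's judgement of risk. The hepatitis B item does not. A site could not waive it for a vaccinated person without departing from the text.
2. **Qualifiers.** Two of the four items carry one: treated latent tuberculosis may be accepted, and hepatitis C antibody counts only with further evidence of virus. The hepatitis B item carries none.
3. **Vaccination.** The only vaccination limit among the medical history criteria concerns live vaccines within 3 months before the first dose. Nothing suggests that immunity from a past vaccine was meant to exclude.
4. **Table 1.** The row confirms that a hepatitis B test is done but not which one, so the laboratory list is the only place where a marker is named.
5. **Liver criteria.** Transaminases above twice the upper limit of normal, and severe, progressive or uncontrolled hepatic disease, are matters of judgement. Neither is a hepatitis B test, and a carrier with enzymes within the limit passes.

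None of these changes the first or the last row.

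**The case against.** The strongest reply is that eligibility is decided by the criteria together. Chronic viral infection is excluded under medical history, and the investigator-opinion wording there attaches to a later item, not to this one. A reader might infer from the laboratory line that the protocol lets active carriers in. The documents do not support that: a carrier who is known, or is found by any test, is ineligible. If local panels included the antigen, which Table 1 neither states nor rules out, a positive result would lead to exclusion by that route. This stands, and it limits the safety gap to the unrecognised carrier.

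It may also be a slip of wording for an antigen test in a condensed article. That is possible, but nothing shown confirms it. The point rests on what the line says, not on detail left to a fuller document.

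A reader might go further and infer that vaccinated people were in fact turned away, that carriers were dosed, or that the sample is skewed towards the unvaccinated. The article has no data on any of these. Any count of lost candidates would rest on an invented vaccination rate, and a loss before randomisation would not bias the comparison between arms.

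Finally, the hepatitis C line is not a perfect model, because it accepts an immunoblot assay as an alternative to polymerase chain reaction, and an immunoblot is itself an antibody assay. So I rely on that line only for what it states: antibody alone is not enough, and presence of virus is the aim.

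**Conclusion.** The point holds in limited form. The only hepatitis B marker named in the article is one of immunity, it is an absolute exclusion, and no other place corrects it. As written, the line excludes immune volunteers and does not detect an unrecognised carrier, so it does not serve the stated aim of keeping out chronic viral infection.

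The size is unknown: how many people were affected, if any, cannot be derived from the article. There is no effect on the sample size of 206, the power or the primary analysis. Because recruitment closed at the end of December 2018, rewording cannot change enrolment. What remains is a safety rule to correct on paper and a safety question to settle from records. The conclusion assumes the usual meaning of the two markers and that sites had no other instruction, which the article cannot show either way.

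**What to change.** Reconcile the laboratory list, the medical history exclusion and the Table 1 row, so that the hepatitis B criterion matches the stated aim of excluding chronic infection. State which marker the sites actually tested. The clinical content of the reconciled rule is for the trial's clinicians to settle.

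Before reporting, check the recorded hepatitis B result, with its marker, for every randomised participant, and the logged reason for every hepatitis B screen failure. This shows whether anyone with evidence of current infection was dosed and whether anyone was turned away for immunity alone, which belongs in the CONSORT account.

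The means already exist. The section on randomisation, blinding and data management has screening data and ineligible candidates entered in the electronic data capture system, and the quality assurance section provides for central and site data checks. If that system holds only positive or negative without the marker, the local laboratory reports are the source. The cost is a wording correction and a records check, with no new sample or visit.
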